## Abstract

**Background:**

Chronic musculoskeletal pain affects more than 20% of the population, and the prevalence is increasing, causing suffering, loss of quality of life, disability, and an enormous expenditure on healthcare resources. The most common location for chronic pain is the spine. Many of the treatments used are mainly passive (pharmacological and invasive) and poor outcomes. The treatments currently applied in the public health system do not comply with the recommendations of the main clinical practice guidelines, which suggest the use of educational measures and physical exercise as the first-line treatment. A protocol based on active coping strategies is described, which will be evaluated through a clinical trial and which could facilitate the transfer of the recommendations of the clinical practice guidelines to a primary care setting.

**Methods:**

Randomised and multicentre clinical trials, which will be carried out in 10 Primary Care centres. The trial will compare the effect of a Pain Neuroscience Education program (six sessions, 10 h) and group physical exercise (18 sessions program carried out in six weeks, 18 h), with usual care physiotherapy treatment. Group physical exercise incorporates dual tasks, gaming, and reinforcement of contents of the educational program. The aim is to assess the effect of the intervention on quality of life, as well as on pain, disability, catastrophism, kinesiophobia, central sensitisation, and drug use. The outcome variables will be measured at the beginning of the intervention, after the intervention (week 11), at six months, and a year.

**Discussion:**

Therapeutic interventions based on active coping strategies are essential for the treatment of chronic pain and the sustainability of the Public Health System. Demonstrating whether group interventions have an effect size is essential for optimising resources in such a prevalent problem.

**Trial registration:**

NCT03654235 “Retrospectively registered” 31 August 2018.

## Background

Chronic musculoskeletal pain (CMP) affects about 20% of the population in western countries [1–3], causing suffering, disability, and a significant loss of quality of life in patients affected by it [3, 4]. It also has a great economic impact related to lost working hours and consumption of health resources [2, 5]. In Primary Care (PC), CMP is one of the most common reasons for consultation, being chronic spinal pain (CSP) the most frequent, and with a growing prevalence [6, 7].

PC has not been giving a satisfactory response to the needs of these patients. General practitioners working in PC devote much of their regular workday to seeing patients with CSP, without being quite certain about what the best therapeutic option is in these cases (Pharmacological and non-pharmacological) [8]. The possibilities for referral are multiple, with no certainty that one option is better than the other such as referral to PC physiotherapy, or referral to different specialised care units (traumatology, rheumatology, neurosurgery, the pain care unit, etc.). Even so, the majority of treatments administered to these patients are focused on the treatment of structures that are considered pain generators (muscles, joints, and stenosis), and in blocking the nociceptive pathways, in both cases with poor results [9]. Therefore, a new therapeutic approach is necessary for the treatment of these patients, and in this sense, advances in neuroscience that have occurred in the past years allow us to know that in CSP, central pain processing mechanisms are involved in the maintenance and perpetuation of the painful experience [10, 11].

The clinical characteristics of Central Sensitisation (CS) presented by the majority of these patients have been meticulously detailed [10, 12, 13]. In addition, structural changes have been reported at the cerebral level, with decreased density and volume of grey matter in prefrontal and dorsolateral cortex, thalamus, brainstem, and somatosensory cortex [14–16], as well as an increase in grey matter volume in the right hippocampus and parahippocampal gyrus [17]. These changes that appear when pain is perpetuated [18], seem to be involved in the dysfunction of the descending inhibitory pathways [10, 19], motor control alterations [20, 21], and the emergence of neural phenomena of long-term potentiation [22] that these patients present. In addition, it is known that patients with CS present kinesiophobia [23], fear-avoidance behaviours [24], disability [2, 25], and high catastrophism levels [26]. Based on this new knowledge, therapeutic approaches are required to reverse or improve the changes described, and in this sense, the most recent clinical practice guidelines recommend patient education and physical exercise in CSP as the first line of action [27–31].

Therefore, a therapeutic approach is necessary to improve functionality, as well as tools to reverse the structural changes that present in some cerebral areas in patients with CSP and CS. Within the educational approach recommended by the guidelines, pain neuroscience education (PNE) as a health education strategy allows changing cognitions by modifying erroneous beliefs and reduces catastrophism, kinesiophobia, and fear-avoidance behaviours [32].

It has been verified that PNE interventions improve their outcomes if they are combined with a physical exercise (PE) directed program [33]. PE is a first-line recommendation in clinical practice guidelines [27–31], and in this sense, aerobic PE has proven to be a great ally in the treatment of CSP [34, 35].

It is also known that certain exercises facilitate neurogenesis, produce neuroplastic changes at the cerebral level [36–39] and activate descending pain inhibitory pathways [40]. In addition, PE improves the functional status of these patients by improving motor control, achieving reduced disability. Therefore, a therapeutic approach based on PNE and a PE directed program, could be a useful tool to improve the quality of life, disability, and to achieve a decrease in perceived pain intensity. With this model that combines PNE and PE, several clinical trials and reviews have been carried out with hopeful outcomes [32, 41–43], but there is great variability in terms of the time dedicated to educational intervention, therapeutic PE program, and the way to perform this exercise program. Most studies on PNE and PE have been carried out in Anglo–Saxon and northern European countries. Taking into account that psychosocial aspects are important in the chronification of pain, and since distinct cultural environments may have a different influence on these psychosocial aspects [44], it is necessary to develop a protocol adapted to our environment (Spain and similar cultures of southern Europe), and conduct a clinical trial to assess the intervention effect. Trials of this kind have not been made yet in PC in our country.

For the reasons shown, a program has been designed based on active coping strategies that include PNE and PE, and that program has been adapted to our healthcare context of PC. The protocol proposed for the evaluation would allow transferring the clinical practice guidelines recommendations to the field of PC, since it has been detected that the clinicians in PC do not have a clear certainty on how to educate CSP patients, and what the best type of PE that can be prescribed. The designed program, which was born and developed in the National Health Service (SNS), in the Castilla y León division (SACYL), aims to optimise the available resources in PC and in order to have a greater reach, we have opted in its design a group intervention which will be described later on. Group interventions have proven to have high therapeutic potential [45–47], and do not exclude that, at the individual level, each patient with CSP can receive specific instructions. In the second part of the program, playful (gamification) and double task components are added to the PE program, aimed at activating new neural circuits which promote neurogenesis and neuroplasticity. In addition, the proposed therapeutic approach encourages the acquisition of healthy lifestyles that can have a beneficial effect on comorbidities, present or potential, in CSP patients (Obesity, HTA, type 2 diabetes, risk of fragility fractures, etc.).

The proposed treatment aims to change cognition and erroneous beliefs in patients with CSP, as well as improve functionality and physical condition. The main objective of the study is to improve the quality of life of patients with CSP. As secondary objectives, the aim is to reduce the levels of catastrophism, kinesiophobia, central sensitisation, disability, and pain intensity. It is also intended to register if the proposed approach decreases the drug consumption and the frequency of the health services for CSP patients. If the results of the intervention are favourable, it is intended, in a second phase of the study, to check for structural and functional changes in brain structures of CSP patients, by using Functional Magnetic Resonance imaging (fMRI) and Diffusion Magnetic Resonance imaging (dMRI).

Therefore, it is proposed to evaluate the effectiveness and cost-effectiveness of a programme based on active coping strategies that include PNE and PE by means of a randomised clinical trial compared to usual care in PC physiotherapy. The protocol outlined describes the characteristics of an educational and physical exercise program, which could be implemented in PC centres of the Spanish National Health Service in case the results are favourable.

## Methods and study design

The clinical trial has been registered (Clinicaltrials.gov NCT03654235) and has received approval from the Ethics Committee of Clinical Investigation (CEIC) of the East Valladolid health area (CASVE-NM _ 16–252) and of the CEIC of the West Valladolid health area (CEIC: 26/17).

This study protocol describes the design of a multicentric randomised clinical trial (RCT) of parallel groups (ratio 1:1) to be carried out in 10 health centres within the Public Health network areas of East Valladolid and West Valladolid, belonging to the public health service of Castilla y León (Spain). The study protocol conforms with the standard protocol items: Recommendations for Interventional Trials (SPIRIT) [48] while the RCT conforms to the Consolidated Standards of Reporting Trials (CONSORT) [49].

Patients will be recruited from family medicine consultations and will be referred to PC physiotherapy units. For patient recruitment, the questionnaire contained in Annex I are used. The RCT flow diagram is shown in Annex I.

### Inclusion criteria

The patients will be recruited from the PC medical consultations in accordance with the following inclusion criteria:
Patients of both sexes between 18 and 70 years old.Non-specific back pain of at least six months (The presence of pain in other regions, in addition to the back, will not be grounds for exclusion)Agree to participate in the study and sign informed consent.

### Exclusion criteria

Oncological pain.Spine fracture or surgical intervention in the previous year.The neurological cognitive alteration that prevents understanding the contents of the PNE program (In case of doubt, assessment with the Minimental test will be conducted [50]. The minimum score is 25 [51])Physical performance deficit that prevents the execution of the planned PE program (Minimum requirement: execution in normal time (10″) of the Timed Up and Go test).Pregnancy.Cauda equina syndrome.Patients presenting other clinical conditions that may aggravate chronic spinal pain (chronic fatigue syndrome, fibromyalgia and complex regional pain syndrome).Patients with associated pathologies that make it impossible to perform a physical exercise program (myopathies, neurological diseases, etc., with significant impairment of functionality)Patients on treatment with alternative therapies.

### Recruitment method

Patients attending family medicine and physiotherapy consultations at the participating centres that meet the inclusion criteria will be invited to participate in the RCT. Physicians and physiotherapists involved in the recruitment process will receive a clinical session to ensure the selection process is carried out in compliance with the inclusion criteria, and that the participants do not meet the exclusion criteria. Patients will receive oral information and a written document (Patient information sheet). If the patient is interested in participating in the study, after signing the informed consent, he will be cited to be evaluated by an external evaluator who will perform the initial assessment. In the same act of the informed consent, the patient will receive a revocation sheet in case they decide to leave the study at any time. After the initial evaluation, participants will be randomly assigned to one of the two study groups (experimental or control).

### Randomisation

After the initial evaluation, each patient will be assigned an alphanumeric code. The alphabetic part of the code will correspond to the participant’s health centre, while the numerical part is allocated by correlative numbers. To perform the randomisation procedure, the Health Technician of the health area of East Valladolid will receive a list of the alphanumeric codes of the participants and make a random allocation using the SPSS statistical package.

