### Sample size calculation

A total of 63 individuals by each group of treatment will allow detecting, in numerical variables, differences between pairs of group mean in a magnitude corresponding to 50% of the standard deviation (an effect size of 50%) with a probability of 80%, keeping the type I error at a 5% level. By taking into account an attrition rate of 25%, it would be necessary to include 78 individuals in each group. The calculation has been done using G*Power 3.1.

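### As described, allocation makes no use of centre although the participant code carries it, and the planned mean comparisons leave centre out; uneven within-centre group sizes and a small loss of precision are avoidable at almost no cost

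*Protocol article*

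**What the plan says.** The protocol article (Methods and study design) describes a "multicentric randomised clinical trial (RCT) of parallel groups (ratio 1:1" design "to be carried out in 10 health centres within the Public Health network areas of East Valladolid and West Valladolid".

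The Randomisation section sets out the steps. After the initial evaluation each patient gets an alphanumeric code: "The alphabetic part of the code will correspond to the participant’s health centre", and the digits are consecutive numbers. The Health Technician of the East Valladolid area "will receive a list of the alphanumeric codes of the participants and make a random allocation using the SPSS statistical package". Nothing is said about strata, blocks or a separate draw for each centre.

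The Statistical analysis section compares means by Student's t or, for clearly non-normal variables, by Wilcoxon–Mann–Whitney. Centre enters neither. Health centre is recorded as a baseline variable. The logistic models for treatment success admit variables through univariate significance and selection procedures, so centre is not assured a place there either.

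Table 1 and the Interventions section describe the experimental exercise as a group programme led by a physiotherapist and applied in the participating centres by trained physiotherapists. No minimum or maximum group size is given.

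**The concern.** Centre matters more here than in a trial of an individually delivered treatment. The physiotherapist and the patient population can differ by centre. The Discussion also presents the group itself as part of what makes the programme work. How many of a centre's patients fall in the experimental arm therefore affects how the programme is delivered there, as well as the arithmetic of the comparison.

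If centre plays no part in the draw, chance alone decides the split within each centre. If centre is then left out of the comparison as well, differences between centres stay in the residual variance and in the chance imbalance between arms. The information needed to prevent both is already in the code that the technician receives.

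**Working it through.** **Inputs.** From the article: 10 centres and a 1:1 ratio (Methods and study design); 63 evaluable and 78 enrolled per group, effect size 0.5 SD, 80% power, 5% type I error (Sample size calculation). Assumptions: two-sided test; equal recruitment, so 156/10 = 15.6 per centre, taken as six centres of 16 and four of 15 (6 × 16 + 4 × 15 = 156); one draw fixed at 78:78.

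**The plan's own figure.** The article states: "A total of 63 individuals by each group of treatment will allow detecting, in numerical variables, differences between pairs of group mean" of "a magnitude corresponding to 50% of the standard deviation (an effect size of 50"%. With n = 2(1.960 + 0.842)²/0.5² = 2 × 7.85/0.25 = 62.8, this gives 63 per group. The figure is reproduced. The exact t-test requires 63.8, so 64, and its power at 63 is 0.795.

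**One centre of 16.** Under a fixed 78:78 draw, the number in the experimental arm is hypergeometric (156 in total, 78 experimental, 16 in the centre).
- Split of 11:5 or worse: 2 × 0.0929 = 0.19
- Split of 12:4 or worse: 2 × 0.0310 = 0.06

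If each patient were allocated by coin toss instead, the first figure would be 2 × 0.1051 = 0.21.

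**Any of the 10 centres**, fixed 78:78 draw, by simulation (20,000 draws). An exact count of all allocations with total 78 agrees to two decimals.

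| Event in at least one centre | Probability |
|---|---|
| Arm difference of 6 or more | 0.79 |
| Arm difference of 8 or more | 0.38 |
| 5 or fewer experimental patients | 0.77 |
| 4 or fewer experimental patients | 0.35 |
| 3 or fewer experimental patients | 0.10 |

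The median of the largest within-centre difference is 7.

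**Sensitivity to centre size.** With assumed sizes 30, 26, 22, 18, 15, 13, 11, 9, 7 and 5 (sum 156), the probability of a difference of 6 or more in some centre is 0.76. The imbalance result does not depend on equal recruitment.

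**With stratification.** In blocks of 4 within centre (block size assumed), the difference in a centre is at most 2, and a centre of 15 to 16 has 7 to 8 experimental patients.

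**Cost in precision when centre is adjusted for.** The information on the treatment difference is the sum over centres of e·c/(e + c), where e and c are the experimental and control numbers. Perfect balance gives 156/4 = 39. Under an unstratified fixed draw the expected fraction of this is (N − K)/(N − 1), with N = 156 patients and K = 10 centres: 146/155 = 0.942, a loss of about 6%. The simulation gives 0.942, with a 5th percentile of 0.893 (a loss of 11%).

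Carrying this fraction over to the evaluable patients gives 63 × 0.942 = 59.3 effective per group. Power by the t-test goes from 0.795 to 0.771, that is, from about 0.80 to 0.77.

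**The case against.** The strongest reply is that the article never says allocation is unstratified. It is a condensed account, and a list of codes that carry the centre letter is just what a per-centre draw would use. This stands as a limit on the wording: the point concerns the procedure as described, and the full protocol may say more. It does not remove the point. The article has a dedicated section that gives the coding scheme, the person responsible and the software, and no step in it uses centre.

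Three stronger readings are tempting, and the documents do not support them.
- **Groups too small to run.** No minimum group size is stated. With equal centres, 3 or fewer experimental patients in any centre has probability of only about 0.10. In small centres stratification would not help: a centre of 5 would still have 2 or 3 experimental patients.
- **Overall arms of unequal size.** A difference of 14 or more between the arms has probability about 30%, but only under coin-toss allocation. A draw fixed at 78:78, which fits the stated ratio and sample size at least as well, keeps the totals equal.
- **A biased estimate.** Unstratified randomisation is valid, and the standard error allows for chance imbalance between arms.

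Clustering from group delivery would exist under stratified allocation too and is a separate matter. It is also true that covariate lists are often left to an analysis plan, which is not shown here. Still, the comparisons that the article does name do not include centre.

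**Conclusion.** The point holds as an avoidable weakness of the described method; it is not an error that invalidates the trial. Under an unstratified fixed draw with about 15 to 16 patients per centre, a clear imbalance in at least one centre is likely: 0.79 for a difference of 6 or more, and 0.77 for 5 or fewer experimental patients. The practical consequence is uneven group sizes in a group-delivered programme. The statistical consequence is modest: about 6% of information and some 2 to 3 points of power when centre is adjusted for.

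The result rests on reading the Randomisation section as a single draw without strata. The group-size figures also rest on equal recruitment across centres. If allocation was in fact done per centre, what remains is to report that and to include centre in the analysis.

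**What to change.** - **Allocation still to be made:** split each centre's codes 1:1, either by randomly permuting each batch of codes from that centre or by concealed permuted blocks of varying size held by the technician. Include centre in the model that compares the arms.
- **Allocation already complete without strata:** leave it, and add centre to the model.
- **Allocation already done per centre:** say so in the Randomisation section, and analyse with centre as the stratification factor.

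The cost is small. The same technician uses the same codes, and the model spends 10 − 1 = 9 degrees of freedom on centre. Block sizes must be kept from recruiting staff.

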### Blinding

All evaluations will be performed by evaluators who do not know the group to which the patient has been assigned. An independent biostatistician will perform the statistical analysis without knowing the treatment carried out by each group. It will not be possible to blind the intervention performed or the physiotherapists who perform it, but physiotherapists who perform the intervention do not participate in the patient evaluation process.

### Interventions

#### A brief descrption of trial's arms are shown in Table 1. The intervention of the experimental group

Patients assigned to the experimental group will perform a PNE program consisting of six sessions (10 h) and 18 sessions of therapeutic PE to be performed in six weeks (18 h), with a frequency of three sessions per week. The program will be carried out according to the order shown in Fig. 1.

**Fig. 1 Fig1:**
[figure not shown]
Temporal distribution of program sessions (experimental group)

**Table 1 Tab1:** A brief description of the trial’s arms

Arms	Assigned Interventions
*Experimental: PNE and PE program* • *Pain neuroscience education (Health education)* • *Physical exercise program*	*Health Education* *Six pain neuroscience education sessions (10 h) and delivery of printed reinforcement material.* *Physical exercise* *Group physical exercise program (18 sessions: three sessions/week) led by a physiotherapist. It includes exercises to improve strength, coordination, balance, and aerobic capacity. Work with double tasks, recreational activities to overcome kinesiophobia and activities to do at home are used in the program.*
*Active Comparator: Usual care in Primary Care Physiotherapy* • *Usual care in Primary Care Physiotherapy Units*	*Usual care in Primary Care Physiotherapy Units* *Treatment supported by the primary care physiotherapy protocol in the health service of Castilla y León that was in force at the time of the intervention. Patients receive 15 sessions of analgesic electrotherapy, thermotherapy and standardised physical exercise.*

PNE is a health education intervention that aims to provide up-to-date information on neuroscience advances in the field of chronic pain. For this purpose, a group educational program has been designed, the contents of which appear in the Additional file 1. Pedagogical resources that facilitate the learning process will be used to enhance knowledge transfer. The times in which patients are merely information receivers, and the times in which they actively participate, will be adequately dosed. Care has been taken with the graphic material that will accompany the presentations, and infographics have been created to facilitate the process. All sessions will use explanatory and motivational videos. The educational intervention will be essential to raise awareness of the need for lifestyle changes and ensure that participants arrive at the second part of the program, which will start the PE, in an “Action Stage”, following the transtheoretical model of Prochaska and Diclemente [52, 53].

PE is carried out in group form, although this will not be an impediment for each participant during the session to receive individualised advice from the physiotherapist. During the sessions, references to the theoretical contents that have been learned in the first part of the program will be made repeatedly. It is essential that patients understand what they do and why they do it. Since patients with CSP have an alteration in their pain inhibitory system [54], the dosage of the scheduled exercise requires taking certain precautions and adapting the exercise dose to the patient’s functional status [34]. The inhibitory system dysfunction may cause an increase in pain during the first PE sessions. Aware of this fact, it will be necessary to be prepared so that this transient increase in symptoms is not lived with alarmism. The appearance of pain during exercise, as long as we move at appropriate levels of intensity, will never be a reason to stop the activity [55, 56]. At all times, during the PE sessions, the increase in functionality is sought as a reference. This aspect will be previously reinforced in the education sessions.

PE sessions will have a basic structure that complies with the recommendations of the American College of Sports Medicine (ACSM) [57], with a warm-up phase, the main part, and a cooling-down part, as can be seen in Fig. 2. This distribution also allows incorporating dual tasks, games, and tasks aimed at stimulating social interaction.

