#### Control group intervention

The control group will receive the standard care treatment carried out in the PC physiotherapy units that is supported by the current physiotherapy protocols in primary care of Castilla y León [58]. The treatment consists of 15 sessions of thermotherapy and analgesic electrotherapy in the area of pain, and the guidelines for the exercises recommended by the SERMEF (Spanish Society of Physic Medicine and Rehabilitation) [59].

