### Statistical analysis

Numerical variables will be summarised with means and standard deviations and categorical ones with percentages. Those numerical variables showing a distribution very far from the normal one will be transformed for getting resulting distributions close to the normal one, or in the opposite case, they will be summarised by using percentiles. For the graphical representation of the numerical variables’ distribution in each treatment group, we will use box and whisker plots. For representing categorical variables, pie charts will be used. In order to test the equality of means for numerical variables, we will apply the Student’s t, if the corresponding distributions are not far from the normal one. In the opposite scenario, we will calculate the Wilcoxon–Mann–Whitney statistics. For testing the association between qualitative variables, we will use Chi-squared statistics, if it is allowed by the observed frequencies in the associated joint distribution. On the contrary, we will re-categorise these variables for reducing them to dichotomous ones, if necessary, and will apply the Fisher exact test. As a function of the observed response to the treatment in numerical variables or the observed change in them, we will build several definitions of success/failure for the result of treatment in individuals. We will fit logistic regression models for predicting the success of the treatment by using the previously mentioned definitions. In these models, those variables which show a statistically significant relationship with the corresponding response variables in the univariate analysis and the variable selection procedures will be included. These models will provide us, as a by-product, odds ratio values for estimating the comparative risk of success associated with each explanatory variable corrected by the presence of the other variables included in them. We will obtain estimates for the sensitivity/specificity of predictive rules derived from these models. It will be considered as statistically significant *p*-values lower than 0.05. Data analysis will be carried by using the R statistical software.

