There is controversy as to whether individual or group treatments are best. In our field of care, due to the high pressure of care and in order to optimise resources, we have opted for group treatment. We take advantage of the fact that the group strategy itself is a very powerful therapeutic tool, as it extols values such as group feelings, stimulates, improves self-esteem, and generates more adherence than the individual strategy [45–47]. However, this does not prevent each participant from receiving individualised guidelines for the therapeutic program.

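### Experimental treatment is given in groups, but the planned tests and the 63 per arm treat patients as independent; any within-group correlation makes p-values too small and power lower than stated

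*Protocol article*

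**What the plan says.** Under Methods and study design, the trial is a "multicentric randomised clinical trial (RCT) of parallel groups (ratio 1:1) to be carried out in 10 health centres". Allocation is by patient: under Recruitment method, "participants will be randomly assigned to one of the two study groups (experimental or control" after the initial evaluation.

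The experimental arm has six education sessions and 18 exercise sessions. For education, the Interventions section says that "a group educational program has been designed". For exercise, it says that "PE is carried out in group form", and Table 1 adds that a physiotherapist leads it. The Discussion explains the choice partly by arguing that "the group strategy itself is a very powerful therapeutic tool".

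For controls, "The treatment consists of 15 sessions of thermotherapy and analgesic electrotherapy in the area of pain", together with exercise guidelines. Nothing describes this as group treatment.

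The Sample size calculation section gives 63 per arm for a difference of 0.5 SD with 80% power and 5% type I error, and adds: "The calculation has been done using G*Power 3.1". It mentions no group size, ICC or design effect. The Statistical analysis section begins its comparisons with "In order to test the equality of means for numerical variables, we will apply the" Student's t, with Wilcoxon-Mann-Whitney as the fallback. Chi-squared or Fisher tests and logistic regression serve the categorical outcomes. It names no term for therapy group, physiotherapist or centre.

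**The concern.** The design is partially nested: experimental patients belong to therapy groups, and controls, as far as the text shows, do not. Patients treated together share sessions, the way the programme is led, and each other's company. If the group contributes to response, as the Discussion argues, some groups will probably do better than others, and outcomes within a group will be correlated.

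The named tests, in their standard form, give each experimental patient the weight of an independent observation. With positive within-group correlation, the variance of the experimental mean is larger than these tests assume. The confidence interval is then too narrow and the type I error rises above 5%. An analysis that allows for the correlation has less power than the 80% stated.

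The primary outcome, the between-group difference in SF-36 change, is exposed to this. The error leans towards a false positive in a trial meant to inform primary care provision. Recruiting more patients into the same analysis would not remove it.

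**Working it through.** **Inputs from the protocol.** Evaluable patients n = 63 per arm; effect d = 0.5 SD; power 80%; alpha 5%; ratio 1:1; 10 centres. Sidedness is not stated.

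**Assumed inputs.** Patients per therapy group, m = 6 to 10; ICC within therapy groups = 0.01, 0.05, 0.10. Neither is in the document. The low end of m follows from one group per centre: 63/10 is about 6. That each centre runs its own group is likely but not stated.

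**Step 1: the plan's own figure.** Normal approximation, two-sided:

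n = 2 × (1.96 + 0.842)² / 0.5² = 2 × 7.849 / 0.25 = 62.8, so 63.

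The exact t-test calculation gives 79.5% power at 63 and 80.1% at 64, so the figure is sound for independent patients. A one-sided test would need only 50. The 63 therefore contains no hidden allowance for clustering.

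**Step 2: formulas with clustering in the experimental arm only.** With equal total variance in the two arms:

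- Design effect in the experimental arm: DE = 1 + (m − 1) × ICC
- True variance of the difference, in SD² units: (DE + 1)/n, where the t-test assumes 2/n
- Understatement of the standard error: √((1 + DE)/2)
- Actual type I error of the t-test: 2 × [1 − Φ(1.96 × √(2/(1 + DE)))]
- Power of a correct analysis: Φ(0.5/√((DE + 1)/n) − 1.96)

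**Step 3: one case in full, m = 10, ICC 0.05.** DE = 1 + 9 × 0.05 = 1.45. The standard error is understated by √(2.45/2) = 1.107. Type I error: 1.96/1.107 = 1.77, giving 7.7%. Power: √(2.45/63) = 0.197; 0.5/0.197 − 1.96 = 0.58, giving 72%. For 80% power, n = 7.849 × 2.45/0.25 = 76.9, so 77 per arm.

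**Step 4: the range, by the same formulas at 63 per arm.**

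| m | ICC | DE | Type I error | Power |
|---|---|---|---|---|
| 6 | 0.01 | 1.05 | 5.3% | 79.2% |
| 6 | 0.05 | 1.25 | 6.5% | 75.4% |
| 6 | 0.10 | 1.50 | 8.0% | 70.9% |
| 10 | 0.01 | 1.09 | 5.5% | 78.4% |
| 10 | 0.05 | 1.45 | 7.7% | 71.8% |
| 10 | 0.10 | 1.90 | 10.4% | 64.4% |

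**Step 5: simulation check of the ordinary t-test.** At ICC 0.01 / 0.05 / 0.10, 10 groups of 6 gave type I error of 5.0% / 6.7% / 8.2%. With 63 patients in groups of 10 (20,000 runs per setting) it was 5.4% / 7.5% / 10.0%. These agree with the formulas to within simulation error. At ICC 0 the test holds its 5%.

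**Step 6: the cost of few groups.** The power formula uses a normal approximation. A valid analysis based on a handful of group means also loses degrees of freedom. Simulated with Satterthwaite degrees of freedom, a group-means analysis gave 77% power with 8 groups of 8 and 73% with 6 groups of 10, both at ICC 0. The second layout also has only 60 per arm. This loss is separate from the correlation and should not be counted as part of it.

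**The case against.** The strongest reply is that nothing in the document shows the correlation to be large, or even above zero. Exercise dose is adapted to each patient and advice is individualised, which could reduce it. At ICC 0.01 the distortion is negligible. With 10 centres, groups of about 6 fit better than groups of 10, and the effect shrinks accordingly. All of this stands. A reader might infer that the p-values are certainly too small; the documents support this only if the ICC is positive.

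A reader might also infer that every experimental patient stays with one fixed group and one physiotherapist through all 24 sessions. The text does not say so: membership is not described, and Table 1 names a physiotherapist only for the exercise.

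Clustering by health centre is a different matter. Both arms come from the same centres, and differences between centres that affect both arms alike do not invalidate the t-test: simulated type I error stayed near 5%. This bears on the remedy. A model with a therapy-group effect but no centre term would count centre variance as group variance. In a group-means check with arms balanced within centre, type I error fell to about 3.3-3.5% at a centre ICC of 0.05, which is over-conservative.

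Finally, this is a condensed article, and a random effect could be left to a full analysis plan. That argument would carry weight if the article were silent on method. It names both the tests and the sample size basis, and neither matches the delivery that it describes.

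**Conclusion.** The concern holds in conditional form. The stated tests and the 63 per arm assume independence, while the experimental arm is treated in groups that the protocol expects to be therapeutic. For any positive within-group correlation, standard errors are too small, type I error is above 5% and a valid analysis has less than 80% power.

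The size depends on assumed values. Taking formula and simulation together for 6 to 10 patients per group, type I error is about 5.0-5.6% at ICC 0.01, 6.5-8% at 0.05 and 8-10.5% at 0.10. Power at 63 evaluable per arm is about 79% / 75% / 71% with groups of 6 and 78% / 72% / 64% with groups of 10, and somewhat lower once the few degrees of freedom are counted.

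This should be fixed. Calling it a fatal flaw would go too far, because the effect ranges from negligible to material and the document cannot say where in that range the trial lies.

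**What to change.** 1. Record a therapy-group identifier for every experimental patient.
2. Replace the simple tests for SF-36 and the other outcomes with a partially nested mixed model. It should include health centre for both arms (already recorded at baseline and coded in the patient identifier), a random intercept for therapy group in the experimental arm only, arm-specific residual variance, and Satterthwaite or Kenward-Roger degrees of freedom. Use the logistic analogue for binary outcomes.
3. State the planned group size and restate the power of this analysis over an ICC range, for example 0.01 to 0.10. Keeping 80% power at groups of 10 and ICC 0.05 would take 77 evaluable per arm. The proposal is to report the lower power openly, and not to enlarge the trial.

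The cost is one extra data field, a slightly wider confidence interval and a lower stated power. Group identifiers can also reveal the arm to the biostatistician, who is to work blind, so the model code should be fixed on dummy identifiers before the real ones are released. Randomisation, recruitment and treatment do not change.
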